#### Moderators and Mediators:

Additional analyses will also be conducted to evaluate whether the effects of zinc depend on level of alcohol consumption. Models will be fit including a zinc by heavy alcohol interaction term. If the interaction is significant (i.e.  $p<0.10$ ), subsequent stratified analyses will be conducted to evaluate the effect of zinc in each alcohol group.

Given the potentially complex role of ART use in the relationship between zinc and each outcome, various analyses will be considered to explore its possible role. First, it is not expected that initiation of ART use during follow-up to differ by randomized arm, however exploratory analyses will be conducted to compare initiation of ART use by randomized group. In addition, longitudinal analyses will be conducted including ART use as a time dependent variable in order to explore a potential zinc by ART use interaction (we will use  $\alpha = 0.10$  to test interaction). If ART use does not appear to be an effect modifier, we will also include it as time will also be included as a dependent covariate to evaluate whether it is a confounder. Lastly, to evaluate ART use as a potential mediator of the relationship between zinc and outcomes of interest, the approach described by Baron and Kenny will be used. To evaluate mediation, the change in magnitude of the zinc effect on our primary outcome, the VACS index (and our other secondary outcomes) in models with and without adjustment for ART use will be focused on. Results will be confirmed using structural equation models (SEMs) to simultaneously model the hypothesized mediated relationships. Fit statistics such as the root mean square error of approximation (RMSEA), Comparative Fit Index (CFI), and the chi-square statistic, will be presented to evaluate the goodness of fit of the SEMs.

To further assess initiation of ART, we will compare proportions initiating of ART by 18 months by randomized group using the chi-square test and also the logrank test to account for drop out/loss to follow-up.

We will also test zinc by heavy alcohol (past week) interaction.

We will test differences in VACS index components between groups.

## 5.5 Harms

The number of participants experiencing each AE/SAE will be presented for each treatment arm and categorized by severity and organ system. No formal statistical testing will be undertaken.

Causes of death will be presented by study arm and time to death will be analyzed using the log-rank test. Cox proportional hazards models adjusted for stratification factors will be used to estimate hazard ratios and 95% confidence intervals.

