### **3.2 RANDOMIZATION**

ZINC randomization will be assigned in a 1:1 ratio to zinc or placebo utilizing block randomization where stratification will be based upon gender and heavy alcohol consumption during the past week to ensure balance. The randomization, stratification and assignment of participants to the two treatment groups will be conducted and monitored by the URBAN ARCH Biostatistics and Data Management (BDM) core. The software package SAS will be used to generate randomization lists to assign participants as they are enrolled into the clinical trial. The study pharmacist will receive the list of randomization IDs with group assignment and will provide packaged boxes of study medication to the study team.

Following completion of the baseline assessment, the RA will be directed to the electronic randomization screen, which will provide a checklist of all components that need to be completed prior to randomization. Randomization will not be able to proceed until all outstanding questions are resolved (e.g., contact information and 7-day alcohol use entered into the electronic system). Once submitted, the randomization page will automatically assign the participant to a randomization ID. The RA will then retrieve the box of study medication labeled with the correct randomization ID and label the box with the participant study ID, thus linking the two numbers. As a double-blinded study, ZINC participants, investigators, RAs and the study nurse will be unaware of participant group assignment.

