**Health**

**NIAAA Award Number: U01AA021989**

**Clinicaltrials.gov Registration: NCT01934803**

**Boston University Medical Campus IRB Protocol Number: H-31901**

**Enrollment Dates: October 2013 – June 2015**

**Statistical Analysis Plan (SAP) Version Date: 10/26/2018**

## **SAP Revision History**

| Date of revision | Section number changed | Description and reason for change                                                                         |
|-------------------------|-------------------------------|------------------------------------------------------------------------------------------------------------------|
| 6/8/2017                | 5.3 Missing Data              | Updating multiple imputation plan to clarify details on specific variables will be included in imputation model. |

|            |                         |                                                                                                                           |
|------------|-------------------------|---------------------------------------------------------------------------------------------------------------------------|
| 8/15/2017  | 5.3 Missing Data        | Adding predictors for missing outcome data.                                                                               |
| 1/26/2018  | 5.1 Outcome Definitions | Posthoc replacement of LPS with IFABP another marker of microbial translocation, due to inability to conduct LPS testing. |
| 2/28/2018  | 5.5 Harms               | Adding posthoc plans for mortality analyses using actual mortality events.                                                |
| 4/13/2018  | 5.4 Additional Analyses | Adding posthoc plans for analyzing individual VACS components.                                                            |
| 10/26/2018 | 5.1 Outcome Definitions | Replacing 16srDNA with LBP, due to the lab having trouble extracting rDNA from study samples.                             |

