# **SECTION 3: STATISTICAL PRINCIPLES**

## **3.1 Confidence intervals and P values**

Statistical tests will be 2-sided and will be performed using a 5% significance test. Confidence intervals will be reported for measures of effect.

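### SAP 5.5 tests time to death with a log-rank test that names no strata, while the hazard ratio beside it is adjusted for the two randomisation factors: valid, but easily aligned

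*Supplement*

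**What the plan says.** SAP 5.5 (Harms) plans no formal testing of adverse events but does analyse deaths. It states that "time to death will be analyzed using the log-rank test", with no mention of strata, and then that "Cox proportional hazards models adjusted for stratification factors will be used to estimate hazard ratios and 95% confidence intervals".

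Protocol 3.2 identifies the factors: "stratification will be based upon gender and heavy alcohol consumption during the past week". SAP 5.2 requires the regression models for the primary outcome to control for both, and carries the same approach over to the secondary outcomes. It sets no rule for log-rank tests; the one for ART initiation in SAP 5.4 also names no strata.

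SAP 3.1 makes tests two-sided at 5%. The revision history dates the mortality analysis to 2/28/2018 and describes it thus: "Adding posthoc plans for mortality analyses using actual mortality events". Death is not among the primary or secondary outcomes in SAP 5.1, and Protocol 2.7.A gives it no power or event target.

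**The concern.** Two analyses are planned for one comparison. The test pools all participants into a single risk set, while the estimate adjusts for gender and past-week heavy drinking. Read as written, the p-value is unadjusted and the interval is adjusted. They can disagree near the 5% line, and the SAP does not say which then governs.

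The test also does not use the randomisation factors, whereas the Cox model beside it and the regression models in SAP 5.2 do. If the factors predict death, a pooled log-rank test after stratified randomisation is somewhat conservative and gives up a little power.

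What is at stake is the clarity of one reported comparison. Because the primary endpoint is a mortality index, readers will look at the actual deaths, and a single unambiguous result helps them.

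**Working it through.** **Figures in the plan.** There is none for mortality: no death rate, event count, hazard ratio or power. The primary-outcome figure does reproduce. With 100 per arm, difference 10 and SD 25, 10 / (25 × √(2/100)) = 2.83, and Φ(2.83 − 1.96) gives 80.7% (80.4% with the t distribution), against the stated 80%. That confirms the design inputs but does not bear on deaths.

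**What differs between the tests.** The unstratified log-rank statistic is Σ(O − E) / √ΣV over pooled risk sets. The stratified one computes O − E and V within each gender-by-drinking cell and then sums. With two binary factors there are four cells.

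**How much the event count matters.** Schoenfeld: power = Φ(|ln HR| × √d / 2 − 1.96). At HR 0.5, |ln HR| = 0.693.

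- d = 10: Φ(1.10 − 1.96) = 19%
- d = 20: Φ(1.55 − 1.96) = 34%
- d = 40: Φ(2.19 − 1.96) = 59%
- 80% power needs 4 × (1.96 + 0.84)² / 0.693², about 66 deaths.

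**Stratified against unstratified, by simulation.** From the documents: N = 250, 1:1 within strata, 18 months, two-sided 5%. Assumed: 30% in the higher-risk gender category, 70% heavy drinking in the past week, 12% censored early, 18-month baseline death risk of 10% or 20%, each factor with the same hazard ratio for death. There were 3,000 runs per scenario, so the Monte Carlo SE of a single rate is √(0.5 × 0.5 / 3000) = 0.9 points at 50%.

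Power at zinc HR 0.5, unstratified → stratified:

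| Factor HRs | About 18–22 deaths | About 36–43 deaths |
|---|---|---|
| 1 | 28.5% → 28.5% | 54.8% → 54.8% |
| 1.5 | 29.6% → 30.2% | 53.4% → 53.6% |
| 2 | 32.0% → 32.4% | 53.0% → 54.5% |
| 3 | 35.3% → 37.2% | 57.8% → 61.4% |

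The differences are 0 to 1.5 points up to a factor HR of 2, and 1.9 and 3.6 points at 3.

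**Type I error.** With no zinc effect, the unstratified test rejected in 3.3% to 4.9% of runs and the stratified test in 4.4% to 5.1%. The 3.3% arose with factor HRs of 3 and about 55 deaths. A separate simulation at factor HRs of 3 gave 3.9–4.2% unstratified and 4.9–5.1% stratified. There is no inflation, and conservatism is visible only when the factors are strongly prognostic.

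**Disagreement between p-value and interval.** In a further simulation (2,000 runs per scenario, zinc HR 0.5), the unstratified log-rank test and the Wald test of the adjusted Cox model gave opposite verdicts at 5% in 1.4% to 4.4% of trials. With factor HRs of 3 and about 35 deaths, stratifying the log-rank test cut this from 3.6% to 1.4%. At about 18 deaths it did not help. A repeat run showed the same pattern, with somewhat more disagreement at the low event count. There the remaining gap is mainly that the log-rank is a score test and the Cox interval a Wald interval.

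**The case against.** The strongest reply is that nothing is wrong. The unstratified test holds its level, and pairing a simple log-rank test with an adjusted Cox hazard ratio is common. The Cox model already handles the strata and yields its own p-value. The analysis is post hoc, sits under Harms and has no power target; with 20 deaths at HR 0.5, power is about 34% whichever log-rank test is used. Where adjustment matters most, SAP 5.2 already requires it. All of this stands, and it is why the point ranks low.

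A reader might infer that the plan gives away real power. The documents do not support that. A gain above about 1.5 points needs both factors near a hazard ratio of 3. Protocol 2.5 admits only people who drank heavily in the past 30 days, so past-week heavy drinking is a contrast among heavy drinkers, and no document gives its effect on death.

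A second objection is technical and also correct. A stratified log-rank test corresponds to a Cox model with a separate baseline hazard per stratum, not to one with the factors as covariates. Stratifying the test alone therefore reduces disagreement with the reported interval but does not remove it. A third is that deaths spread over up to four cells can leave some with little information.

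What survives is the mismatch itself: one comparison, two treatments of the randomisation factors, no reason given, and no statement of which result governs.

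**Conclusion.** The point holds as a minor improvement. SAP 5.5 pairs a log-rank test that names no strata with a Cox model adjusted for the two randomisation factors. The test is valid, and slightly conservative only if those factors strongly predict death. Stratifying brings about 0 to 1.5 points of power for factor HRs up to 2, about 2 to 4 points if both are near 3, and possibly nothing with few deaths. These sizes rest on assumed death risks, factor prevalences, factor effects and a zinc HR of 0.5, none of which the documents supply.

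Two stronger readings should be resisted. The unstratified test does not inflate the false-positive rate: it rejected in at most 4.9% of null runs. Nor does the choice affect a main conclusion of the trial, since no primary or secondary outcome uses this test. The number of deaths limits the mortality comparison far more than stratification does. The case for the change is mainly consistency.

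**What to change.** In SAP 5.5, specify that the log-rank test for time to death is stratified by gender and past-week heavy alcohol consumption. Then bring the p-value and the interval together in one of two ways:

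- Stratify the Cox model by the same factors. Test and estimate then share one model, with only a score-versus-Wald difference left.
- Keep the covariate-adjusted Cox model and take the reported p-value from it. Its Wald p-value then agrees exactly with its Wald interval.

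State which result governs. The cost is a sentence in the SAP and one STRATA statement in SAS, with a dated line in the revision history. If deaths have already been compared by arm, report the stratified result beside the test as written and label it accordingly. The downside is that, with few deaths, sparse strata contribute little and the stratified test may gain nothing.

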## 5.6 Statistical Software

Data will be analyzed with SAS version 9.4 (SAS Institute, Inc., Cary, NC).
